**Summary**:

Since December 2019 COVID-19 is dominating the life of the people of this universe. Its behavior also varied among the nations of the universe. The risk factor of adverse outcome of COVID-19 was determined. No biologic markers for the susceptibility of the infection is yet to be found. The relation of blood group and infection was found in several disease like cholera, severe malaria, severity of dengue, H-pylori infection have been elucidated. Genome wide Association Study of Severe Covid-19 with Respiratory Failure, GWAS Group detected cross-replicating associations with rs11385942 at locus 3p21.31 and with rs657152 at locus 9q34.2. The association signal at locus 9q34.2 coincided with the ABO blood group locus. Several studies also found some contradicting results in this regard.

So to observe the impact of ABO blood groups on the presentation and outcome of Confirmed COVID -19 infection, this study was conducted in the largest COVID19 dedicated hospital in Bangladesh. It would be a prospective cohort study. A cohort of the patients with RT-PCR positive COVID-19 patients since June 2020 till September 2020 will be included in this cohort. Their blood group will be determined. The clinical features, severity, time required to recover, conversion of severity, Persistence of RT-PCR positivity 14 days after initial positivity will be determined. They will be followed up for at least 30 days or hospital discharge which one is longer. Comparison will be made in different blood groups.

The primary outcome would be the duration required to have clinical improvement.

Data will be analyzed using SPSS 20. To compare the groups one way ANOVA was done for continuous variable, Chi square for categorical variables. For outcome assessment relative risk (RR) with 95% CI was measured for qualitative variable categorizing blood group A and non A. survival analysis by Kaplan-Meier curve was done for the duration of recovery. Result of the study and statistical analysis will be presented by tables, figures, graphs, diagrams, charts and photographs. All these will have own legends (i.e. title) and will be serially numbered. Discussion will be done on the basis of result obtained from the study and comparing with similar studies done at home and abroad. Summarization will be drawn after discussion. Conclusion will be drawn depending upon the results and discussion.

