**3. RATIONALE:**

Covid-19 is an emergent pandemic, threatens the life of millions of the people throughout the globe. The severity, outcome and susceptibility varies among the nations, race and individuals. Biologic markers of COVID-19 infection is still uncertain. Several studies revealed blood group A is most susceptible. The studies were performed with the affected patients only. This study Aim to observe the impact of different blood groups on presentation and outcome of confirmed COVID-19 infection. It would help us to detect a biologic marker for the susceptibility and outcome of COVID-19 infection.

1. **METHODOLOGY:**

Study type: Prospective cohort

Sample size:

Proportions to cure from COVID-19 by day-12 in group-1(blood group A) and group-2 (blood group Assuming expected B, O, AB) are 0.70 and 0.90 respectively. Thus we need a total of 378 samples at 1:2 ratio, and, that would provide a power of at least 90% at two tailed test where p value less than 0.05 to detect significant difference between the groups. Considering 10% dropout, we need 416 samples in total.

$$n=\frac{r+1}{r}\frac{p^{*}\left( 1-p^{*} \right){(Z_{\beta}+Z_{\frac{\alpha}{2}})}^{2}}{{{(p}_{1}- p_{2})}^{2}}$$

r = ratio of group-1 and group - 2

p*= Average of proportion

Z_α/2_ = Level of significance

Z_β_ = Power of the test

p_1_ - p_2_= Effect size

p_1_ = Proportion in group - 1

p_2_ = Proportion in group - 2

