**Primary Outcome Measure:**

- 1. Duration required to have clinical improvement

[Time Frame: 1 months]

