**Data analysis**:

To compare the groups one way ANOVA was done for continuous variable, Chi square for categorical variables. For outcome assessment relative risk (RR) with 95% CI was measured for qualitative variable categorizing blood group-A and non-A (Group-B, AB, O). Survival analysis by Kaplan-Meier curve was done for the duration of recovery.

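### The study is sized on day-12 cure, which is not a listed outcome, and the A versus non-A contrast behind that sizing is never attached to the primary outcome, a duration to clinical improvement

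*Protocol*

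**What the plan says.** **Outcome.** The Summary states: "The primary outcome would be the duration required to have clinical improvement". The Primary Outcome Measure section lists "Duration required to have clinical improvement" with "Time Frame: 1 months", and Part-G repeats it. Clinical improvement is defined by five criteria under Operational definition.

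**Sizing.** The Sample size text under Methodology, repeated in Part-G, starts from "Proportions to cure from COVID-19 by day-12 in group-1(blood group A") and the other groups combined. The two proportions "are 0.70 and 0.90 respectively", and the conclusion is "we need a total of 378 samples at 1:2 ratio", with power of at least 90% at two-sided 0.05. Day-12 cure is not among the primary or secondary outcomes, and cure has no definition.

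**Analysis.** The Data analysis section, repeated in Part-G, has three sentences. The first is general: "To compare the groups one way ANOVA was done for continuous variable, Chi square for categorical variables". The second gives a relative risk with 95% CI for A versus non-A, for qualitative variables. The third is "Survival analysis by Kaplan-Meier curve was done for the duration of recovery". It does not say which groups the curves compare, and recovery is not defined either.

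**The concern.** Three terms stand for the main event: cure (sizing), clinical improvement (outcome) and recovery (analysis). Only the second is defined. The only power statement belongs to a two-proportion comparison on an endpoint that is not listed, while the listed primary outcome gets a curve. The A versus non-A contrast is restricted to qualitative variables, so it does not reach a duration.

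A reader cannot tell which comparison is confirmatory: day-12 improvement in A versus non-A, the time curves, or a comparison of mean durations across blood groups. That choice could be made after the data are seen.

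There is also a question of estimation. A duration is a continuous variable, so the general ANOVA rule could be read to cover it. ANOVA needs an observed duration for every patient. Anyone who has not improved within the window, has died or has dropped out lacks one. Leaving out the unimproved removes the slowest recoveries, more of them in the slower group.

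**Working it through.** **Inputs from the protocol:** day-12 proportions 0.70 (A) and 0.90 (non-A); total 378 at 1:2, that is 126 + 252; two-sided 0.05; power 90%; outcome window one month, taken as 30 days. z values: 1.960 and 1.2816, so (1.960 + 1.2816)² = 10.507.

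**Assumptions added here, not in the protocol:** proportional hazards for the hazard ratio; constant hazards (exponential recovery) for anything after day 12; all 378 patients followed to day 30.

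**1. The plan's own figure.** The printed formula with p* = 0.80 and r = 0.5 gives 3 × 0.16 × 10.507 / 0.04 = 126.1; three times 126 is 378. With r = 2 it gives 1.5 × 0.16 × 10.507 / 0.04 = 63.0, a total of 189. So 378 is reached only by taking r = 0.5 and treating the result as the smaller group. That is a separate matter. Here it means that 126 + 252 gives 99.6% power for 0.70 versus 0.90, so the claim of at least 90% is true for that two-proportion test.

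**2. The same planning values on the time scale.**
- Hazard ratio, A versus non-A: ln(0.30)/ln(0.10) = 0.523, with log −0.648 and squared log 0.420.
- Events for 90% power (Schoenfeld): 10.507 / [(1/3)(2/3) × 0.420] = 112.5, so 113.
- Daily rates: −ln(0.30)/12 = 0.1003 and −ln(0.10)/12 = 0.1919.
- Improved by day 30: 1 − exp(−30 × rate) = 95.07% and 99.68%.
- Expected events: 126 × 0.9507 + 252 × 0.9968 = 119.8 + 251.2 = 371.
- Log-rank power with 371 events: above 99.9%.
- Hazard ratio detectable with 90% power: exp(−√(10.507 / (0.2222 × 371))) = 0.70.

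Counting only events to day 12, which needs no constant-hazard assumption, there are 126 × 0.70 + 252 × 0.90 = 315. Power is still above 99.9% and the detectable hazard ratio is 0.68.

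**3. If ANOVA were applied to improvers only.** With S = exp(−30 × rate), the unimproved share at day 30 is 4.9% in A and 0.3% in non-A.

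| Mean days | Formula | A | Non-A | Difference |
|---|---|---|---|---|
| Restricted to 30 days | (1 − S)/rate | 9.48 | 5.20 | 4.28 |
| Improvers by day 30 only | 1/rate − 30·S/(1 − S) | 8.41 | 5.12 | 3.30 |

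Shortfall: 1 − 3.30/4.28 = 23%, towards no difference.

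**The case against.** **The survival sentence governs the duration.** The Data analysis section gives the duration its own method, and a specific sentence normally overrides a general one. The case record form holds many laboratory values to which ANOVA naturally applies. This stands. A reader might infer that the primary outcome will be tested by ANOVA on improvers only, but the protocol never applies ANOVA to the duration and never says that unimproved patients are dropped. The 23% shows what an open reading would cost; it is not a result of the plan.

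**The test can be left to a SAP.** A log-rank or Cox analysis, and the censoring rule, may be specified in a statistical analysis plan that is not shown. This stands for the missing test taken alone, so a reader should not infer that the primary outcome will go untested. It does not cover the mismatch, because no SAP can make the sizing endpoint agree with the listed outcome without departing from the protocol.

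**Unimproved patients may still have a duration.** Follow-up runs for at least 30 days or to discharge, whichever is longer, so some late improvements would be seen. This stands in part: the outcome window is one month and the daily grids on the form end at day 30.

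**Power is intact.** A reader might infer from the mismatch that the study is underpowered. The protocol's own values show the opposite. Even the improvers-only comparison would be significant with near certainty: model SDs of 7.1 and 4.9 days with about 120 and 251 improvers give a standard error of 0.72 and z of about 4.6.

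**The terms may be loose wording for one event.** That is possible, and a day-12 proportion can be read off the same Kaplan-Meier curve. The protocol does not say so, and only clinical improvement is defined.

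**Conclusion.** The point holds in a limited form and is a should-fix. Established from the text alone: the primary outcome is a duration, the only power statement concerns an unlisted and undefined day-12 cure, and the A versus non-A effect measure is confined to qualitative variables. As written, the protocol does not make the contrast that sized the study on its primary outcome.

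The damage is to which comparison is confirmatory and how it is estimated, not to power. The planning values need about 113 events on the time scale, against 315 to 371 expected.

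The possible attenuation of about 23% depends on exponential recovery through 0.70 and 0.90 at day 12, and on an improvers-only ANOVA that the protocol permits by a literal reading but does not prescribe. Set against the unrestricted mean difference (9.97 − 5.21 = 4.76 days) the shortfall would be 31%, but a one-month outcome does not support that comparison.

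**What to change.** 1. **Name one primary comparison:** a log-rank test with a Cox hazard ratio and 95% CI for A versus non-A, on time to clinical improvement as defined under Operational definition. Censor at day 30, keep patients who die as not improved to day 30, and use the Kaplan-Meier curve as the display.
2. **State one time origin.** The case record form records symptom onset, positivity and admission dates, and its daily grids start at admission. Which to use is the sponsor's choice, but it must be fixed.
3. **State that ANOVA does not apply to the duration.**
4. **Keep the four-group comparison as a stated additional analysis,** since the Specific objectives include differences between blood groups.
5. **Use one term** in place of cure, improvement and recovery.
6. **Align the sizing.** Either restate it as a hazard ratio and number of events (0.52 and 113 on the present values, or 0.70 as the effect detectable with about 371 events), or list day-12 clinical improvement as a named outcome, analysed by the relative risk already planned.

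The cost is wording in the Summary, Sample size, Primary Outcome Measure and Data analysis sections and their Part-G copies, plus the outcome list if day 12 is kept. The form already has daily records to day 30, so no new daily visits are needed, and the sample size need not rise.

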**Demography**

1. Name: 2. Age: 3. Sex: M / F

4. Address:

5. **Epidemiological link**: Y / N

5. Mobile No:

6. Residency: Urban / Rural

7. Smoker: Y / N

8. Marital Status: Married / Single

9. Education: Literate / Illiterate

Date of starting symptoms

Date of becoming Covid positive

Hospital Admission Date

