**Obsrvation**

| Trait |  | Follow-up  Yes-1, No-2 | | | | | | | | | | | | |
| --- | --- | --- | --- | --- | --- | --- | --- | --- | --- | --- | --- | --- | --- | --- |
|  | On Admission | D2 | D3 | D4 | D-5 | D-6 | D-7 | D-8 | D-9 | D-10 | D-11 | D-12 | D-13 | D-14 |
| Temperature |  |  |  |  |  |  |  |  |  |  |  |  |  |  |
| Pulse rate |  |  |  |  |  |  |  |  |  |  |  |  |  |  |
| BP |  |  |  |  |  |  |  |  |  |  |  |  |  |  |
| Respiratory Rate |  |  |  |  |  |  |  |  |  |  |  |  |  |  |
| Oxygen saturation |  |  |  |  |  |  |  |  |  |  |  |  |  |  |
| Co- Morbidity | DM/HTN/ IHD/ HF/ CKD/CLD/Asthma/COPD/Malignancy/ CTD | | | | | | | | | | | | | |

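### Every analysis named for this non-randomised cohort is unadjusted although the main prognostic covariates are on the CRF, and deaths before improvement have no stated rule

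*Protocol*

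**What the plan says.** The design is stated as "Study type: Prospective cohort". The Data analysis section, which recurs in the Summary of Part C and in the ethics committee abstract of Part G, names four methods. Two are general tests: "To compare the groups one way ANOVA was done for continuous variable, Chi square for categorical variables". The third is an effect measure for binary outcomes, a risk ratio with its interval that sets group A against the other three groups pooled. The fourth concerns the primary outcome: "Survival analysis by Kaplan-Meier curve was done for the duration of recovery".

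None of the three places names a covariate, a stratum or a regression model. The primary outcome is the time needed for clinical improvement, over one month. Entry is limited to adults with mild to moderate disease, enrolled consecutively at one hospital.

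The CRF collects age, sex, smoking and "Date of starting symptoms" under Demography, and a comorbidity list, "DM/HTN/ IHD/ HF/ CKD/CLD/Asthma/COPD/Malignancy/ CTD", under the observation table. Death is not a listed outcome. The CRF as shown has an admission date but no field for death, discharge or final status, and the protocol gives no rule for a patient who dies before improving.

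**The concern.** Blood group is not allocated by the study. A crude difference in recovery between A and non-A can therefore reflect a difference in age, comorbidity or stage of illness at admission. Age, sex and smoking do not cause blood group, so imbalance has to come from elsewhere, such as ancestry or selection into the cohort.

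The entry rule gives one concrete route. The Introduction reports a higher risk of severe disease in group A. If that is so, excluding severe cases removes more of the A patients with poor prognosis, and those who remain look better on other factors. That would mask an adverse effect of group A.

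The Rationale hopes to find a biologic marker of outcome, which a crude contrast supports poorly. A Kaplan-Meier curve by itself also yields no adjusted effect estimate for the primary outcome.

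Separately, when recovery is the only event counted, a common default is to censor a patient at death. This treats the patient as someone who would have recovered later.

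**Working it through.** **Inputs from the protocol (sample size section).** Recovery by day 12 "are 0.70 and 0.90 respectively" for A and non-A; "we need a total of 378 samples at 1:2 ratio", hence 126 and 252; two-sided 5%; power at least 90%.

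**Assumed, because the documents give no figure.** Strength of a prognostic score (log-hazard per SD) 0.3 to 0.7; systematic imbalance between groups 0 to 0.4 SD; 30-day deaths 1% to 10%.

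**1. The plan's own figure.** n = ((r+1)/r) × p*(1−p*) × (Zβ+Zα/2)² / (p1−p2)². With r = 0.5 and p* = 0.80, n = 3 × 0.16 × 10.507 / 0.04 = 126.09, and 3 × 126 = 378. The number reproduces when n is read as the smaller group. With r = 2 the formula gives 63 + 126 = 189, so 378 is generous for this effect.

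**2. Power at the planned effect.** The two-proportion test at 126:252 for 0.70 versus 0.90 has 99.6% power. With exponential recovery the implied hazard ratio is ln(0.3)/ln(0.1) = 0.523. In simulated Cox models (1000 runs per setting, censoring at day 30, no systematic imbalance, score strength 0.3 or 0.6), power is 99.3% to 100% unadjusted and 100% adjusted. At a smaller effect, HR 0.70, it is 84% (strength 0.3) or 70% (strength 0.6) unadjusted, against about 88% adjusted.

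**3. Bias at the null (true HR 1).**

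| Imbalance | Score strength | Unadjusted HR | False positives, unadjusted | False positives, adjusted |
|---|---|---|---|---|
| 0 | 0.3 to 0.6 | 1.00 | 5% to 6% | 5% to 7% |
| 0.2 SD | 0.3 | 0.95 | 8% | 5% |
| 0.2 SD | 0.6 | 0.91 | 13% | 5% |
| 0.2 SD | 0.7 (baseline hazard 0.10/day) | 0.90 | 17% | 5% |
| 0.4 SD | 0.3 to 0.6 | 0.89 to 0.83 | 17% to 37% | 5% |

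The rows at 0.3 and 0.6 use a baseline hazard of −ln(0.1)/12 = 0.192 per day. The adjusted HR is about 1.00 in every row.

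**4. How large an imbalance could selection produce?** Assume an odds ratio of 1.5 to 2 for severe disease in group A, an odds ratio of 2 to 4.5 per SD of the score, and 15% to 30% excluded as severe. Group A among those enrolled is then about 0.03 to 0.10 SD lower on the score. At strength 0.6 the upper end shifts the log hazard by 0.6 × 0.10 = 0.06, an HR of about 1.06. This is modest and smaller than the 0.2 SD rows.

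**5. Deaths.** With constant hazards h (recovery) and d (death), a curve that censors deaths shows 1 − exp(−30h) recovered at day 30. The true cumulative incidence is h/(h+d) × (1 − exp(−30(h+d))). For group A, h = −ln(0.3)/12 = 0.100, so the curve shows 95.1%. The true figures are:

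- 1% deaths: 94.2%
- 2% deaths: 93.4%
- 5% deaths: 90.8%
- 10% deaths: 86.5%

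The overstatement is 0.9, 1.7, 4.3 and 8.6 points. For non-A (curve 99.7%) it is 1.0, 2.0, 4.9 and 9.9 points.

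**The case against.** The strongest objection is that covariates, censoring rules and the handling of deaths commonly belong in a statistical analysis plan, which is not at hand; not naming adjustment is not ruling it out. This stands for the details. It does not dispose of the point, because the protocol sets out its methods in three places and every one is unadjusted. A CRF without a death field is also something that a later analysis plan may be unable to repair.

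Four stronger readings are tempting and are not supported:

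- **That the result will be confounded.** Blood group is fixed at birth, the documents give no imbalance data, and with no systematic imbalance the unadjusted test holds its level.
- **That the study loses power.** At the planned effect it does not. A balanced covariate also moves the unadjusted HR from 0.70 to about 0.76 in simulation, but that is non-collapsibility: the marginal and conditional ratios are different quantities. The plan names no HR, and the relative risk that it does name is collapsible.
- **That the protocol censors deaths.** It states no rule; censoring is an inference. Because entry is limited to mild to moderate disease, deaths may be few.
- **That ANOVA and Kaplan-Meier compete for the primary outcome.** The last sentence of Data analysis assigns duration of recovery to Kaplan-Meier, and the specific sentence reasonably governs.

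It is also fair to say that the stated aim is to observe association, for which a crude comparison is informative. It should stay, beside an adjusted one.

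**Conclusion.** The point holds as a worthwhile improvement to the stated method, not as a flaw that invalidates the study. All named analyses are unadjusted in a non-randomised, hospital-selected cohort whose CRF already holds the obvious covariates.

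If the groups differ systematically by 0.2 SD on a prognostic score of strength 0.3 to 0.7, the unadjusted HR under no effect is about 0.90 to 0.95, with 8% to 17% false positives; adjustment for that score restores about 5%. Both the imbalance and the score strength are assumptions. Adjustment gains power only for effects smaller than planned, about 4 to 18 points at HR 0.70.

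The handling of deaths is unstated. If they were censored, day-30 recovery in group A would be overstated by about 1 to 2 points at 1% to 2% deaths, and by about 4 to 9 points at 5% to 10%.

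**What to change.** - **Primary outcome.** Add a Cox model of time from enrolment to clinical improvement, A versus non-A. Adjust at least for age and sex, with smoking, comorbidity and days from symptom onset to admission as further prespecified covariates. Report the unadjusted result beside it.
- **Relative risks.** Use modified Poisson regression (robust variance) with the same covariates, again beside the crude RR.
- **Deaths.** Add a death date and final status to the CRF, taken from the hospital records that the protocol already plans to use. Count patients who die before improving as not improved to day 30, keep them in the risk set until then, and plot cumulative incidence. The ratio then describes the subdistribution hazard, which should be stated.
- **Sensitivity analysis.** Show a model with age and sex only, because comorbidity may partly lie on the causal path from blood group to outcome.

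The cost is a little more analysis and one or two CRF fields; no new covariate data are needed. The downside is that missing covariates need a stated method of handling.

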**Observation and Results:**

Result of the study and statistical analysis will be presented by tables, figures, graphs, diagrams, charts and photographs. All these would have own legends (i.e. title) and will be serially numbered.

**Discussion:**

Discussion will be done on the basis of result obtained from the study and comparing with similar studies done at home and abroad.

**Summary:**

Summarization will be drawn after discussion.

**Conclusion:**

Conclusion would be drawn depending upon the results and discussion

**Conflict of interest:** None

**Operational definition:**

**(According to WHO and National guideline)**

**Confirmed Covid-19:**

Cases with positive RT-PCR for Covid 19 irrespective of symptoms**.**

**Uncomplicated (mild) Illness**

These patients usually present with symptoms of an upper respiratory tract viral infection, including mild fever, cough (dry), sore throat, nasal congestion, malaise, headache, muscle pain, or malaise. Signs and symptoms of a more serious disease, such as dyspnea, are not present.

**Moderate Pneumonia**

Respiratory symptoms such as cough and shortness of breath (or tachypnea in children) are present without signs of severe pneumonia.

